### Secondary intervention

Patients in both the primary groups are randomised to either a short 'telephone call' or 'no telephone call' after they have completed the 4-month follow-up assessment. Patients who receive 'no telephone call' are treated as usual, which imply that they can contact the outpatient clinic if they have additional questions or comments. Patients who receive the 'telephone call' are asked the following three questions: "how are you doing?", "did you receive the help you needed for your OA when you were at the hospital?", and "do you want to add any further information concerning your health status and the treatment given"?

### Recruitment procedure

All referrals from general practitioners to the outpatient clinic with focus on OA are screened for eligibility according to the inclusion and exclusion criteria. A research coordinator contacts patients who are potentially eligible for the study by telephone, inform them about the study and ask whether they want to participate. In the same telephone contact, a screening tool for classification of OA is used in the cases in which an OA diagnosis was evident based on information in the referral letter [16]. If the OA diagnosis cannot be clinically confirmed during the examination by the rheumatologist during the first appointment, the participant will be excluded. Written consent according to the declarations of Helsinki is obtained before enrolment to the study. In addition, they are sent the first questionnaire by mail to be filled in before the first appointment at the outpatient clinic.

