## Methods

Patients are randomised into the two interventions within three strata: patients with primary hand, hip or knee problems. A project coordinator includes patients and coordinates the patient-reported data collection with questionnaires. Health professionals who are taking part in the two interventions are not involved in the data collection. Blinding of providers and patients is not possible in this type of study, but the outcome assessors as well as those who perform the follow up telephone call are blinded. All patients involved in the project have signed an informed consent and have been informed according to the Helsinki declaration. The data inspectorate and the regional ethical committee (REK) reviewed and approved the project (REK ref 156-06073 1.2006.598); the ISRCTN trial number is 25778426.

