### Primary intervention

The *experimental intervention *is a multidisciplinary and multifaceted intervention, in which the referred patients first receive a 3.5 hour group-based educational programme, and thereafter individual consultations with a rheumatologist and other members of the multidisciplinary team, dependent on identified needs. The multidisciplinary team consists of rheumatologists, an orthopaedic surgeon, nurses, health secretaries, physiotherapists, occupational therapists, a pharmacist and a dietician.

The group-based educational programme contains four main themes identified through qualitative interviews with patient advocates. The themes are: a) What is OA? b) Activity possibilities or limitations, what can we do ourselves? c) Treatment options and d) How to live with OA.

The *control intervention *is regular care in an individual outpatient clinic. The patients are referred to and examined by a rheumatologist. According to usual procedures they are referred to other specialists or health professionals such as orthopaedic surgeons, physiotherapists, occupational therapists etc. dependent on identified needs. The access to health care providers is in principle similar to the access in the experimental group, but encounters occur according to referral.

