### Group allocation

All patients are randomly allocated to one of two groups, experimental or control group. This randomisation is performed after completion of the baseline questionnaires. To ensure equal-sized treatment groups, random permuted blocks of 4-8 participants are used [17]. The stratified random allocation schedule is computer generated by a statistician who is not otherwise involved in recruitment, assessment or treatment of participants. The randomisation sequence is carried out in sequentially numbered, opaque, sealed envelopes.

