#### Statistical analyses

Primary data analysis will be performed in a blinded manner, by conducting the effect analyses without knowing which intervention each of the two groups received. The treatment groups will be examined for baseline comparability. Both parametric and nonparametric statistical analyses will be used, dependent on how the variance is distributed. Effect of the interventions will be analyzed according to intention-to treat principles. Further, exploratory analyses will be performed to study the treatment effect within the three subgroups hip, knee and hand OA.

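### Exclusion for an unconfirmed OA diagnosis falls after randomisation, rests on an unblinded provider's judgement, and conflicts with the unqualified intention-to-treat statement

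*Protocol article*

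**What the plan says.** All of the following is in the protocol article.

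- **Recruitment procedure.** Consenting patients receive the baseline questionnaire by post: "they are sent the first questionnaire by mail to be filled in before the first appointment at the outpatient clinic". The exclusion rule is: "If the OA diagnosis cannot be clinically confirmed during the examination by the rheumatologist during the first appointment, the participant will be excluded".
- **Group allocation.** "This randomisation is performed after completion of the baseline questionnaires". The first appointment is not named as a precondition.
- **Primary intervention.** Experimental patients "first receive a 3.5 hour group-based educational programme, and thereafter individual consultations with a rheumatologist". For the control arm: "The patients are referred to and examined by a rheumatologist". The Background describes the same order, education and then consultation, for the multidisciplinary clinic.
- **Methods.** "Blinding of providers and patients is not possible in this type of study".
- **Statistical analyses.** "Effect of the interventions will be analyzed according to intention-to treat principles". No exception and no modified analysis set is given.
- **Subjects.** Eligibility requires that a specialist has confirmed the clinical diagnosis.
- **Screening.** Recruitment procedure says that, by telephone, "a screening tool for classification of OA is used in the cases in which an OA diagnosis was evident" from the referral letter. The Discussion describes a screening form based on clinical criteria without that restriction, and says that a rheumatologist and the project coordinator go through all referrals.

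**The concern.** Randomisation makes the two groups comparable as randomised. A rule that removes patients afterwards keeps that comparability only if it removes the same kind of patient at the same rate in each arm. Here the decision is made at the treatment visit, by someone who knows the allocation. In the experimental arm the patient has by then already attended the education session.

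Both primary outcomes are exposed. A patient told that the complaint is not OA may plausibly be less satisfied at 4 months, so removing more such patients from one arm would flatter that arm. For cost-effectiveness at 12 months, the resource use and EQ-5D change of removed patients disappear. Yet seeing some patients whose diagnosis is not confirmed is part of what either clinic model costs in a pragmatic comparison. If exclusion also ends follow-up, no later analysis can recover those outcomes.

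**Working it through.** **Order of events.**

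1. The baseline questionnaire is to be completed before the first appointment (Recruitment procedure).
2. Randomisation follows completion of the questionnaire (Group allocation).
3. In the experimental arm, group education comes before the rheumatologist (Primary intervention). A patient cannot be sent to the education session before being allocated to it, so allocation precedes the examination in that arm.
4. In the control arm, the rheumatologist's examination is itself the start of the allocated care. Steps 1 and 2 place allocation before it.
5. No separate diagnostic visit before allocation is described.

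The exclusion is therefore applied to patients who have already been randomised. No sentence says so outright; it follows from these sections together.

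**Safeguards.** Excluding ineligible patients after randomisation can be defended when eligibility is judged on pre-randomisation information, blind to allocation and by one rule for both arms. The article provides for none of these.

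**Size.** The plan gives no exclusion rate and no expected difference in satisfaction, so there is no figure of its own to reproduce. The inputs below are assumptions, apart from the 200 patients per arm (Power calculations).

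Let e1 and e0 be the proportions excluded in the two arms, with a true effect of zero. The gap between excluded and other patients can be defined in two ways:

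- Excluded patients score g SD below *retained* patients. The retained mean then exceeds the full mean by g × e, and bias = g × (e1 − e0).
- Excluded patients score d SD below the mean of *all randomised* patients. The retained mean then exceeds the full mean by d × e/(1 − e), and bias = d × [e1/(1 − e1) − e0/(1 − e0)].

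With a gap of 1 SD:

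| Excluded | Gap to retained | Gap to all randomised |
|---|---|---|
| 5% v 5% | 0 | 0 |
| 10% v 5% | 0.10 − 0.05 = 0.05 SD | 0.111 − 0.053 = 0.058 SD |
| 15% v 5% | 0.15 − 0.05 = 0.10 SD | 0.176 − 0.053 = 0.124 SD |

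A gap of 0.5 SD halves these figures.

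**Effect on the test.** This uses the first definition, a two-sided 5% z-test and 200 randomised per arm. The standard error in SD units is √(1/n1 + 1/n0), where n is the number retained.

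- 10% v 5%: 180 and 190 retained, SE = 0.104. The type I error is 7.7% for a gap of 1 SD and 5.7% for 0.5 SD.
- 15% v 5%: 170 and 190 retained, SE = 0.106. The type I error is 15.7% for a gap of 1 SD and 7.6% for 0.5 SD.
- 5% v 5%: the type I error stays at 5%.

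The effect on cost-effectiveness is not quantified, because the article gives no cost or utility figures to work from.

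**The case against.** **Timing is inferred.** The design figure is not shown. The Discussion also lets a project assistant help with the questionnaire at the first encounter, so some patients might complete it, and be randomised, only then. That is fair, and it makes the order less certain in the control arm. It does not change the order in the experimental arm, where education still precedes the examination.

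**Exclusion is not defined.** The rule does not say whether the patient leaves treatment, follow-up or analysis, and an analysis plan that is not shown might define the analysis set. The plain reading is that the patient leaves the study. If follow-up stops, no analysis plan can restore the data. If something narrower is meant, the text has to say so.

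**OA status predates randomisation.** A 3.5-hour session cannot change whether a patient has OA, so bias needs the examiner's judgement to differ by arm. This stands: no section shows that it does, and bias is possible rather than established. What is missing is any protection against it.

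**Three stronger readings are not supported.**

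- A reader might infer that different rheumatologists serve the two arms. The article does not say so; only setting and sequence differ.
- A reader might infer from the telephone-tool wording that doubtful cases are randomised without screening. Recruitment procedure has all referrals checked against the eligibility criteria, and the Discussion adds a rheumatologist's review and an unrestricted screening form. The sections are inconsistent, and the restriction may be a drafting slip. Review before the call also suggests that unconfirmed cases may be few.
- A reader might set the bias against the difference behind the sample size, 0.20/0.70 = 0.286 SD (printed as 0.25). That is a WOMAC/AUSCAN pain effect. No satisfaction effect was planned, so a percentage of it has no meaning here.

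**Conclusion.** The point holds. As written, the plan excludes randomised patients on an unblinded provider's judgement, and this conflicts with its unqualified intention-to-treat statement. It should be corrected because it touches the randomised comparison for both primary outcomes.

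The supportable claim is that the rule can bias these comparisons, not that it does. The illustrative bias in satisfaction runs from zero, with equal exclusion of similar patients, to about 0.10 to 0.12 SD with 15% v 5% excluded and a 1 SD gap. The exclusion rates and the gap are assumptions with no basis in the article. The conclusion also rests on the inferred order of events, which is firm for the experimental arm and likely for the control arm.

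**What to change.** 1. Replace the exclusion rule. From now on, every randomised patient stays in follow-up and in the primary intention-to-treat analysis by allocated group.
2. Record each diagnosis not confirmed at the first appointment, report the numbers by arm, and leave these patients out only in a sensitivity analysis.
3. Reword the specialist-confirmation criterion under Subjects so that it is applied to information available before randomisation (referral review and telephone screening), by the same rule in both arms. Without this, keeping unconfirmed patients would contradict the eligibility criteria.
4. Reconcile the telephone-tool wording in Recruitment procedure with the screening form in the Discussion.

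The cost is a protocol amendment, continued follow-up of patients who would otherwise leave, one sensitivity analysis, and slight dilution from a few patients without confirmed OA. Data collection is already under way, so patients excluded so far may lack follow-up. Their numbers should be reported by arm, and the limitation stated.

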### Group allocation

All patients are randomly allocated to one of two groups, experimental or control group. This randomisation is performed after completion of the baseline questionnaires. To ensure equal-sized treatment groups, random permuted blocks of 4-8 participants are used [17]. The stratified random allocation schedule is computer generated by a statistician who is not otherwise involved in recruitment, assessment or treatment of participants. The randomisation sequence is carried out in sequentially numbered, opaque, sealed envelopes.

**Figure 1 F1:**
[figure not shown]
**Design and assessments in the study**.

## Outcome measures

Table 2 provides an overview of the various questionnaires used at data collection at baseline, after 4 and 12 months.

**Table 2 T2:** Questionnaires and assessments in the study

	At inclusion	4 mnd	12 mnd
Socio-demographic data			
Age, gender, height, weight, marital status	X		
Work situation (profession, % of full time)	X		
Education	X		
Smoking	X		
Physical activity	X		
Earlier and current treatments	X		
Co-morbidities	X		
Pain and functioning			
Pain during the last week (NRS 0-10)	X	X	X
WOMAC/AUSCAN	X	X	X
PSFS	X	X	X
Self-efficacy/ASES	X	X	X
Health related quality of life			
SF-36	X	X	X
EuroQoL	X	X	X
Satisfaction with care			
Satisfaction with care (numeric rating scale 0-10)		X	X
Various data at follow-up			
Use of health care and services (diary)		X	X
Global question on change of health status		X	X

NRS = Numeric Rating Scale

SF-36 = Short Form-36 health survey

WOMAC = Western Ontario and McMaster Universities Osteoarthritis Index 3 AUSCAN = Australian/Canadian Osteoarthritis Hand Index

PSFS = Patient-Specific Functional scale

ASES = Arthritis Self Efficacy Scale

### Primary outcomes

The primary outcome measure is patient satisfaction with the health service, which will be evaluated on a 11 point numeric rating scale (NRS) from 0 = not satisfied to 10 = very satisfied [18]. The co-primary outcome is c*ost-effectiveness*, which will be based on changes in utility-scores based on EQ-5D in the denominator [19] and direct and indirect costs related to OA in the numerator. The costs will be assessed by recording the use of health care by patient self-report. All patients will receive a diary and all consultations and costs related to OA care during the follow-up will be recorded in this diary. Indirect costs related to the disease, like sick leave, lost working days and the use of social security will also be included in this cost-effectiveness analysis.

### Secondary outcomes

Secondary outcomes are pain and global disease activity, generic and disease specific functioning and disability using the component summary scales in the SF-36 health survey, WOMAC, AUSCAN, a patient-generated measure of disability (PSFS), and global perceived effect of change in health status during the study period.

*Pain *is measured on a NRS (range 0-10) with the anchor words 'no pain at all' and 'unbearable pain'. *Global disease activity *is measured on a NRS (0-10) with the anchor words 'no symptoms' and 'extremely severe', answering the question: "All symptoms taken into account, what do you think about your condition the last week?"

Health related quality of life is measured by the generic questionnaire SF-36 [20]. The SF-36 Health Survey is a widely used generic instrument that comprises eight health scales that contribute to two higher order health scales, the Physical Component Summary (PCS) and Mental Component Summary (MCS) summary scores which give a mean (SD) of 50 based on normative data from the general population (Ware, 1995). The SF-36 is often used to assess health related quality of life in the general population and in different diseases. The English version has been translated to and validated in Norwegian [21].

Disease specific functioning in daily life is assessed by the WOMAC [22] for patients with hip or knee OA. This instrument is responsive and valid for measuring pain (5 items), stiffness (2 items) and physical function (17 items). The Likert scale version of the scale is used with response options none, mild, moderate, severe, extreme.

For patients with hand OA disease specific health problems are self-reported by the AUSCAN, which comprises 15 items relating to hand stiffness (one item), pain (five items) and problems with performance of activities (nine items). This study used the five-point descriptive scale version of the AUSCAN with response options none, mild, moderate, severe, extreme [23].

Through the use of the *PSFS*, all patients will also be asked to describe the three most important activity limitations caused by their OA and score each of these on a 0-10 point scale according to the ability to perform these activities [24]. Patients will be interviewed regarding their activity limitations during the telephone interview at baseline before randomisation.

The *global perceived effect of change *in health status during the study period will be assessed on a 5-point scale ranging from much better through unchanged to much worse.

*Self-efficacy *will be evaluated using the Arthritis Self Efficacy Scale (ASES) for pain and functioning [25].

### Baseline questionnaire

All patients are asked to fill in a questionnaire at inclusion, containing information on socio-demographics (age, gender, height, weight, marital status, work situation, emotional distress and physical activity), earlier and current pharmacological and non-pharmacological treatment for their OA and co-morbidities. They are also asked to complete standardised instruments for measurement of pain; functioning and health related quality of life.

Additional therapies and co-interventions are also registered. Patients who withdraw from the study will be registered by a research secretary. Delivery of interventions in both groups will be registered by the health professionals responsible for the intervention. Registering co-interventions will be part of the diary.

### Data analysis

#### Power calculations

As no satisfactory data on patient satisfaction and cost-effectiveness were available, power calculations were based on the secondary outcome pain with data from the pilot study and previous research on OA from our group [26-28]. In this RCT we compare two independent equally sized groups. We assume comparable variation in both groups, set alpha to 5%, beta to 80%, and assume a smallest clinical important difference between the groups of 0.20 based on an estimated difference for pain measured by WOMAC/AUSCAN. The standardized difference (0.20)/SD (0.70)) will be 0.25. According to the Altman nomogram, approximately 200 patients will be needed in each of the two treatment groups.

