### Study sample and setting

A total of 400 participants referred to an outpatient hospital rheumatology clinic with a diagnosis of hip, knee, hand and/or generalized OA, will be recruited for the study.

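### The sample-size paragraph labels the 80% as beta; it can only be the intended power, and the power of 200 per group depends on a sidedness and a standardized difference that the text does not settle

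*Protocol article*

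**What the plan says.** The Power calculations section of the protocol article sizes the trial on pain, a secondary outcome, because the authors had no adequate data on satisfaction or cost-effectiveness. Its inputs are:

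- **Design:** "we compare two independent equally sized groups".
- **Error rates:** "set alpha to 5%, beta to 80" per cent. Whether alpha is one-sided or two-sided is not stated.
- **Target difference:** the authors "assume a smallest clinical important difference between the groups of 0.20", on WOMAC/AUSCAN pain.
- **Standardized difference:** "The standardized difference (0.20)/SD (0.70)) will be 0.25".
- **Result, read from a nomogram:** "approximately 200 patients will be needed in each of the two treatment groups".

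The Study sample and setting section gives the matching total: "A total of 400 participants referred to an outpatient hospital rheumatology clinic". Nowhere else does the article give a value for power or for the type II error.

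**The concern.** Beside alpha in a power calculation, beta is the probability of missing a true difference of the target size. Taken literally, the sentence plans a trial that misses its target four times in five. That does not fit a requirement of 200 per group, which is several times what such a design would need.

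The stake is whether the justification for 400 patients can be reproduced. The phrase is the article's only stated operating characteristic, so nothing else in the text corrects it. It also stands next to a standardized difference that does not equal the ratio it is said to come from, so a reader who wants to recover the inputs behind 200 cannot take the printed figures at face value.

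**Working it through.** **Inputs, all from Power calculations:** alpha 0.05; difference 0.20; SD 0.70; printed standardized difference 0.25; equal groups; n = 200 per group. From the raw inputs, d = 0.20/0.70 = 0.286. Because sidedness is not given, both cases are shown.

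**Formulas (normal approximation, equal groups):**

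- n per group = 2 × (z_alpha + z_power)² / d², rounded up
- power = Φ(d × √(n/2) − z_alpha)

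Here z_alpha is 1.960 two-sided or 1.645 one-sided, and z_power is 0.842 for 80% power or −0.842 for 20% power.

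**Step 1. Can the printed 200 be reproduced with the 80% read as power?**

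- Two-sided, d = 0.286: 2 × (1.960 + 0.842)² / 0.0816 = 2 × 7.849 / 0.0816, giving 193.
- Two-sided, d = 0.25: 2 × 7.849 / 0.0625, giving 252.
- One-sided, d = 0.25: 2 × (1.645 + 0.842)² / 0.0625 = 2 × 6.183 / 0.0625, giving 198.
- One-sided, d = 0.286: 2 × 6.183 / 0.0816, giving 152.

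Two combinations come close to 200: two-sided at 0.286 (193) and one-sided at 0.25 (198). A ratio cut to 0.28, two-sided, gives 201. The article does not show which was used.

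**Step 2. Can it be reproduced with beta literally 80% (power 20%)?**

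- Two-sided, d = 0.286: 2 × (1.960 − 0.842)² / 0.0816 = 2 × 1.251 / 0.0816, giving 31.
- Two-sided, d = 0.25: 2 × 1.251 / 0.0625, giving 41.
- One-sided: 16 at 0.286 and 21 at 0.25.

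No combination comes near 200. Two-sided, the printed number is 200/41 = 4.9 to 200/31 = 6.5 times what a beta of 80% would need.

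**Step 3. What do 200 per group deliver?** With n = 200, √(n/2) = 10.

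| Alpha 5% | d | Argument of Φ | Power | Beta |
|---|---|---|---|---|
| Two-sided | 0.286 | 2.857 − 1.960 = 0.897 | 81.5% | 18.5% |
| Two-sided | 0.25 | 2.500 − 1.960 = 0.540 | 70.5% | 29.5% |
| One-sided | 0.25 | 2.500 − 1.645 = 0.855 | 80.4% | 19.6% |
| One-sided | 0.286 | 2.857 − 1.645 = 1.212 | 88.7% | 11.3% |

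A two-sample t-test calculation agrees for the two-sided rows: power 81.3% at 0.286 and 70.3% at 0.25.

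**The case against.** The strongest reply is that this is a slip of wording that no informed reader would take literally. The phrase stands under a heading about power, 80% is a natural value for power, and nothing in the trial would be run differently if it were corrected. Most of that stands. The 31 or 41 per group shows only that the literal reading was not the one used; it does not measure any harm to the design. But a guessable intention does not make the stated figure right, and the article offers no second statement to fall back on. Nor is this detail that an article leaves to a fuller document: the value is given, and given wrongly.

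A second reply concerns the replacement value, and it stands in full. A reader might infer that the true beta is simply about 20%, two-sided, so that swapping the label completes the repair. The article does not support that. It never says that alpha is two-sided, and at its own printed 0.25 a two-sided test with 200 per group has a beta of 29.5%. A one-sided test at 0.25 fits the printed number about as well as a two-sided test at 0.286. If the label alone were changed and alpha described as two-sided with 0.25 left in place, the paragraph would claim 80% power where it has about 70%.

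**Conclusion.** The point holds as a labelling error. A beta of 80% contradicts the printed 200 per group under every combination of sidedness and standardized difference tried, so the 80% can only be the intended power. That conclusion does not depend on resolving the 0.25 against 0.286 discrepancy; the value to put in its place does. Power at 200 per group is about 81% (two-sided, 0.286), about 80% (one-sided, 0.25) or about 70% (two-sided, 0.25).

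A reader might also infer that the trial is planned with 20% power, or that its sample size is wrong because of this phrase. Neither follows: the 200 per group was plainly not derived from 20% power, and the label has no effect on enrolment.

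The figures assume a comparison of two means with a common SD, equal groups and 200 analysed per group. They describe power for pain, the outcome used for sizing, and not for either co-primary outcome. The matter is minor.

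**What to change.** Replace the beta statement with power 80% (beta 20%). In the same sentence, state whether alpha is one-sided or two-sided and which standardized difference was taken to the nomogram, so that label, ratio and sample size agree. The sponsor has to confirm these from its own records, since the article fits more than one set of inputs:

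- two-sided with 0.20/0.70: print the ratio as 0.286 (power about 81% at 200 per group);
- one-sided with 0.25: say that alpha is one-sided, and correct the difference or SD so that they give 0.25 (power about 80%);
- two-sided with 0.25: state the power as about 70%, and correct the difference or SD likewise.

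The cost is one sentence in the sample-size paragraph. The planned 400 patients stay as they are.

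### The printed standardized difference of 0.25 does not match its own inputs: 0.20/0.70 is 0.286, and about 200 per group follows from 0.286, not from 0.25

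*Protocol article*

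**What the plan says.** The Power calculations section bases the sample size on pain measured by WOMAC/AUSCAN, because no satisfactory data were available for patient satisfaction or cost-effectiveness. Its inputs are:

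- **Design:** "we compare two independent equally sized groups".
- **Variance:** "We assume comparable variation in both groups".
- **Error rates:** "set alpha to 5%, beta to 80" per cent. Sidedness is not given.
- **Difference:** the authors "assume a smallest clinical important difference between the groups of 0.20".
- **Ratio:** "The standardized difference (0.20)/SD (0.70)) will be 0.25".
- **Result, read from the Altman nomogram:** "approximately 200 patients will be needed in each of the two treatment groups".

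Study sample and setting gives the matching total: "A total of 400 participants referred to an outpatient hospital rheumatology clinic".

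**The concern.** Three of the printed numbers cannot all be right: a difference of 0.20, an SD of 0.70 and a ratio of 0.25. The nomogram is entered with the ratio, so a reader who trusts the printed 0.25 will find that 200 per group falls well short of 80% power. A reader who divides 0.20 by 0.70 will find that it is enough. This is the only sample-size justification in the document, and it does not show which value was used.

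The answer affects how the results can be read. Hypothesis 4 predicts no difference between the groups in the secondary outcomes, including pain, WOMAC and AUSCAN. A non-significant result on the outcome used for the power calculation would fit that prediction, and the weight it can bear depends on whether the trial had about 81% or about 70% power.

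The statement on beta is a separate slip. Beta is the type II error rate, so a beta of 80% would mean 20% power.

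**Working it through.** **Inputs.** From Power calculations: difference 0.20, SD 0.70, printed ratio 0.25, alpha 5%, 1:1 allocation, common SD, 200 per group. Power is taken as 80%, because a literal beta of 80% would need only 31 patients per group (at 0.286) or 41 (at 0.25), far from 200. A two-sided test is assumed first because the section does not state sidedness.

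**1. The ratio.** 0.20 / 0.70 = 0.286. To obtain 0.25, either the SD must be 0.20 / 0.25 = 0.80 or the difference must be 0.25 × 0.70 = 0.175. The section gives neither value.

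**2. Sample size for 80% power, two-sided 5%.** Normal approximation: n per group = 2 × (1.96 + 0.8416)² / d² = 15.70 / d².

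- d = 0.286 (0.20/0.70 unrounded): 15.70 / 0.08163 = 192.3, so 193. The t-test gives 193.3, so 194. This reproduces the plan's approximate 200.
- d = 0.25: 15.70 / 0.0625 = 251.2, so 252. The t-test gives 252.1, so 253. This does not reproduce it.

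**3. Power with 200 per group, two-sided 5%.** Power ≈ Φ(d × √(200/2) − 1.96) = Φ(10d − 1.96).

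- d = 0.286: Φ(2.857 − 1.96) = Φ(0.897) = 81.5% (t-test 81.3%).
- d = 0.25: Φ(2.50 − 1.96) = Φ(0.54) = 70.5% (t-test 70.3%).

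The ratio that 200 per group detects with exactly 80% power is (1.96 + 0.8416) × √(2/200) = 0.280. That is close to 0.286, so 200 is a plausible nomogram reading for the stated difference and SD.

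**4. One-sided reading.** At one-sided 5% and d = 0.25, n = 2 × (1.645 + 0.8416)² / 0.0625 = 197.9, so 198 per group (t-test 198.5, so 199). Power at 200 is 80.4% (t-test 80.3%). On this reading 0.25 and 200 agree with each other, but 0.20/0.70 still does not equal 0.25.

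**5. Reserve at 0.286.** 1 − 194/200 = 3.0% by the t-test, or 1 − 193/200 = 3.5% by the normal approximation. The document gives no loss rate. As an illustration only, with assumed losses of 10, 15 and 20%, the analysed groups are 180, 170 and 160, and power at 0.286 is about 77, 75 and 72%.

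**The case against.** The strongest reply is that nothing of substance is wrong. The stated difference and SD give 193 to 194 per group, the plan says approximately 200, and that delivers about 81% power. On this view 0.25 is a misprint on the way to a sound sample size, for a calculation on a secondary outcome. Most of that stands, and it limits the point to an inconsistency in the stated figures. It does not remove the inconsistency, because the document does not show whether the ratio or one of its inputs is the misprint.

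Several stronger readings are tempting, and the document does not support them:

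- **That the sample size is wrong, or that the trial has 70% power rather than 80%.** The 70% requires both that 0.25 was intended and that the test is two-sided. If 0.20 and 0.70 are right, it does not apply. A one-sided 5% test would also reconcile 0.25 with 200, although no such test is stated and Hypothesis 4, which expects no difference, does not suggest a directional one.
- **That the calculation uses an outcome outside the plan, because pain is defined on a 0–10 scale.** WOMAC and AUSCAN are also listed under Secondary outcomes, with their pain items, and Power calculations says that the difference is for pain on those instruments.
- **That power for the primary outcomes was overlooked.** The section gives the reason for its absence.
- **That losses will bring power below 80%.** No loss rate is stated, and an article may leave a dropout allowance to the full protocol. The figures under loss are illustrations.

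**Conclusion.** The point holds as an internal contradiction in the power paragraph. The printed standardized difference is 0.25, and its own inputs give 0.286. About 200 per group follows from 0.286 (193 to 194 needed, about 81% power at 200) and not from 0.25 (about 252 needed, about 70% power at 200). These figures assume a two-sided 5% test, equal groups and a common SD. The beta statement is also wrong and must mean power of 80%.

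The likelier explanation is that 0.25 is the misprint, since the other inputs reproduce the sample size, but the document cannot settle this. On that reading the 400 patients suffice when nearly all are analysed.

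**What to change.** Rewrite the power paragraph as follows:

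- Correct the standardized difference to 0.29 (0.286 before rounding). If 0.25 was intended, correct instead the difference or SD that produces it, for example an SD of 0.80, and restate the power at 200 per group as about 70%.
- State that the test is two-sided.
- Replace the beta statement with power of 80% (beta 20%).
- State that about 81% power at 0.286 applies to 200 analysed per group, with about 3% in reserve for loss. An illustration may be added, labelled as such: about 77% power at an assumed 10% loss and 72% at 20%.

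Keep 400 patients. The cost is one paragraph, with no change to design or analysis. The stated power may become less favourable: slightly so if losses are shown, and by about 10 percentage points (80% to 70%) if 0.25 was the intended value.
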